### Feedback and psychoeducation procedure

Patients will receive individual feedback first. The feedback is inspired by psychoeducation procedures [17]. For each diagnosis for which a positive result is found, patients are first prompted about their knowledge of the disorder, and then given their test results. Test results will involve diagnoses and possible treatment options and implications (e.g., psychotherapy and/or medication for anxiety/depression; skills training and/or medication for attention deficit/hyperactivity disorder). For personality disorders, treatment implications, resources and relevant treatment options are summarized in Table 2.

**Table 2 T2:** Treatment implications, personal resources, and relevant treatment options for each of the ten personality disorders

**Personality disorder**	**Implications**	**Resources**	**Treatment options**
Paranoid	Problems dealing with high expressed emotion; needs time to build trust; needs great patience; problems with groups, especially confrontative groups.	Careful, able to cope in realistic danger; protects own privacy	Counselling; inpatient treatment in small wards with great flexibility; not exploratory psychotherapy [10]
Schizoid	Problems dealing with high expressed emotion; needs great patience; does not benefit from requests for participation in social activities.	Able to deal with being alone;	Counselling; possibly inpatient treatment in small wards with great flexibility [10]
Schizotypal	Problems dealing with high expressed emotion; needs great patience; problems with groups; needs time to build trust.	Creative, independent thinking	Counselling; possibly inpatient treatment in small wards with great flexibility [10]; antipsychotic medication
Antisocial	Impulse actions; "plays the game"; needs straight talk from counsellor or case worker; transgresses boundaries in treatment;	Great potential for action under many circumstances	Therapeutic community or similar treatment [33]; regular addictions treatment; cognitive-behavioural interventions, or similar
Borderline	Impulse actions; transgresses boundaries in treatment; needs to learn to cope with emotion; chaotic relationships to therapists	Sensitive and able to experience emotions	Psychotherapeutic treatment; antidepressants; antipsychotics; inpatient treatment; long-term involvement
Histrionic	Flirts and appears shallow and superficial to others; has difficulties focusing on own situation and issues	Charming and outgoing	Psychotherapeutic treatment; counselling; inpatient treatment; cognitive-behavioural interventions
Narcissistic	Appears grandiose and arrogant; makes it difficult for staff members to intervene ("scares" away all criticism)	Has ability to feel pride	Inpatient treatment for drug misuse; self-change program, cognitive-behavioural interventions
Avoidant	Difficulty getting out with new people; stays in "safe zones", and has difficulty trying out new treatment options or seeking social support or employment	Self-protective; sometimes able to stay out of trouble by keeping away	Psychotherapeutic treatment; antidepressants; inpatient or outpatient treatment; individual counselling and case management
Dependent	At high risk of abusive relationships	Good ability to form working relationships; good compliance	Psychotherapeutic treatment; antidepressants; inpatient or outpatient treatment; individual counselling
Obsessive-compulsive	Difficulties concluding in counselling or therapy settings; attempts to control counsellor, and other professionals	Sticks to goals	Psychoeducation;

### Follow-up procedure

Trained interviewers will make contact with study participants before randomization, but after intake interview. Interviewers will be blinded to randomization status. The follow-up interview will contain the same elements as the baseline interview (i.e., the K6, the ASRS, the WSAS, the OTI, and the SDS). Also, patients will be asked to rate the value of the feedback procedure on visual analogue scales representing the skills of the interviewer (on a line ranging from "extremely unskilled" to "extremely skilled"), his knowledge (from very little knowledge, to highly knowledgeable), his degree of interest in the patient, his understanding of the patient, the value of the feedback for the treatment, the value of the treatment for the patient, how much thought the patient has given the feedback, and how much work he has done in regard to the issues discussed in the feedback.

Finally, the patient is asked to rate his alliance with the caseworker using the Working alliance inventory, patient version [29].

At each interview point, the caseworker is asked to rate the patient using the clinical global impression scale with anchor points for alcohol and drug abuse [23], externalizing behaviour [23], and GAF [23], and to complete the Working Alliance Inventory, clinician version [29].

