## Background

Substance use disorders and personality disorders often co-occur [1,2]. Patients with personality disorders are commonly seen in treatment programs for substance abuse, consume a disproportionate amount of staff time, and are more likely to drop out from substance abuse treatment interventions [3,4].

At the same time, therapists and other professionals tend to react negatively to patients with personality disorders at an emotional level [5], this is especially the case with cluster B (dramatic/erratic) personality disorders [6].

Even if patients with personality disorders benefit from treatment, they often remain more symptomatic than patients without personality disorders, and remain at a lower level of functioning [7,8].

Therefore, treatment that meets the needs of patients with substance abuse and personality disorders is needed. Recently, some studies have shown that integrated treatment for personality disorders and substance abuse may be superior to treatment that focuses solely on substance abuse treatment [9-11].

This randomized experimental study is designed to assess whether systematic assessment of personality disorders improves outcomes, vs. assessment of Axis I disorders alone.

The objective of this study is to estimate the effect of routine assessment of co-morbid axis II disorders in a centralized intake unit for substance use disorders.

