**Figure 2 F2:**
[figure not shown]
Flowchart of participants.

**Table 1 T1:** Instruments at different assessment moments

	Baseline	Follow-up	Follow-up
Interview:			
SAPAS [22, 23]	*	*	*
ASRS [14]	*	*	*
K6 [32]	*	*	*
OTI [15]	*	*	*
SDS – alcohol [21]	*	*	*
SDS – drugs [21]	*	*	*
WAI [29]		*	
Ratings of the feedback procedure – VAS		*	
Clinician rated:			
CGI-externalizing [23]		*	*
CGI-substance use [23]		*	*
GAF [23]		*	*
WAI [29]		*	

**Notes**: *SAPAS*: Standardised Assessment of Personality – Abbreviated Scale. *ASRS*: Adult ADHD Self-Report Scale. *K6*: Kessler 6. *OTI*: Opiate Treatment Index. *SDS*: Severity of Dependence Scale. *WAI*: Working Alliance Inventory. *VAS*: Visual analogue scales. *CGI*: Clinical Global Impression. *GAF*: Global Assessment of Functioning.

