### Data handling and record keeping

Patient information will only be accessible to the research team. All data will be link-anonymised so that no patient identifying information will be kept with raw data. All files will be kept with the local research teams in a locked and secure cabinet. Electronic data will be stored on a central computer at the research centre.

A personal feedback letter will be given to the patient, in which the patient appears only with his or her first letter. If the patient agrees that the information in the personal feedback should be shared with the caseworker, then the same letter will be given to the caseworker. Raw data will, however, only be kept and stored by the Centre for Alcohol and Drug Research.

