## Discussion

This paper describes the study protocol of a randomized controlled trial concerning personality disorder assessment and feedback versus an open interview. The aim of this study is to assess the potential value of personality disorder assessment for referral and casework in a real-life setting. The study design described above has specific strengths and limitations.

The study has a single-blind design, where patients are unaware if their treatment is designated as an "experimental" or "control" treatment. Follow-up interviewers are blinded to allocation, and we have procedures to reduce the risk that follow-up interviewers are made aware of subjects' status (i.e., follow-up interviewers make contact with patients before randomization is known; patients are told not to disclose details about the interview to the follow-up interviewers).

The study uses an attention placebo design, which means that the effects of time and attention are controlled for. Research has shown strong assessment reactivity in substance use outcome [20], meaning that patients who are exposed to assessment show improvement only for that reason. The amount of contact is controlled for in this trial. This means that if significant effects are found, they give strong support to the efficacy of personality disorder assessment.

The setting in which the study takes place is a community service. This means that although training and supervision is provided for caseworkers, the caseworkers are not primarily working with the research project. While this may reduce the potential efficacy of the intervention, it means that the study is in a sense between an efficacy trial and an effectiveness study.

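### The follow-up interview that collects the primary scales also asks patients about their feedback, which puts interviewer blinding at avoidable risk; caseworker ratings are open-label wherever the letter is shared

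*Protocol article*

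**What the plan says.** **Blinding of interviewers.** Follow-up procedure states "Interviewers will be blinded to randomization status". Randomization and blinding makes the same claim, and the Discussion repeats it: "Follow-up interviewers are blinded to allocation, and we have procedures to reduce the risk". The Discussion names two safeguards: interviewers meet patients before allocation is known, and "patients are told not to disclose details about the interview to the follow-up interviewers".

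**Content of the follow-up interview.** Follow-up procedure places K6, ASRS, WSAS, OTI and SDS in the interview, then adds that "patients will be asked to rate the value of the feedback procedure on visual analogue scales representing the skills of the interviewer". The last of the ratings is "how much work he has done in regard to the issues discussed in the feedback". Table 1 puts "Ratings of the feedback procedure" in its block of interview measures, marked for the first follow-up only.

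**Caseworkers.** At the follow-up points they rate CGI, GAF and the clinician version of the alliance inventory (Follow-up procedure). If the patient consents to sharing the personal feedback, "then the same letter will be given to the caseworker" (Data handling and record keeping).

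**Primary outcome.** Outcome criteria lists four areas, including treatment engagement scored by staff. Outcome evaluation lists three: K6, WSAS and OTI substance use.

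**The concern.** Blinding at 3 and 6 months depends on the patient not telling the interviewer what the second interview and the feedback were about. The protocol asks for that silence, and then has the same interviewer ask how the feedback was received and what the patient has done about it. A patient who answers naturally may name a personality disorder diagnosis, or describe a summary of his life situation. Either would disclose the arm.

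The three scales common to both statements of the primary outcome are collected in this interview. An interviewer who knows the arm can influence probing and scoring, and the resulting bias would be indistinguishable from an effect of the intervention.

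Staff ratings raise a separate question. A caseworker who has read the letter knows what kind of assessment the patient had, and then supplies ratings that will be compared between arms.

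**Working it through.** No arithmetic beyond counting applies. The document gives no figure from which a bias could be computed, so the check sets its sections side by side.

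1. **Does having feedback reveal the arm?** No. Under Design, patients in both conditions receive feedback. Axis I results are assessed at baseline in everyone, so a remark about anxiety or ADHD is uninformative. SAPAS is also given to everyone at baseline, so a passing mention of personality is not conclusive either.

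2. **Does the content of the feedback reveal the arm?** Yes, if voiced. In the experimental arm the second interview assesses Axis II disorders, and diagnoses are fed back with the treatment implications of Table 2. In the control arm the feedback contains a condensed summary of a client-driven interview. A named personality disorder diagnosis, or an account of that summary, would identify the allocation.

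3. **Do the rating items ask for content?** There are eight. Four concern the interviewer (skill, knowledge, interest, understanding). One concerns the value of the treatment to the patient. Three concern the feedback itself (its value for treatment, thought given to it, work done on it): 4 + 1 + 3 = 8. None asks the patient to state what the feedback said. The last, on "how much work he has done in regard to the issues discussed in the feedback", comes closest to inviting it.

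4. **Do the safeguards cover this?** Meeting the interviewer before randomization does not prevent disclosure months later. That leaves the instruction to patients, and the rating items work against it.

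5. **Which primary data are exposed?** There are two waves, and the ratings occur at the first.
   - If the ratings follow K6, WSAS and OTI, the first wave is already complete. The exposure falls on the second wave, 1 of 2 (50% of scheduled primary assessments), provided the same interviewer returns.
   - If the ratings precede the scales, the first wave is exposed too.
   - Follow-up procedure mentions the scales first and the ratings afterwards, but does not fix an order.
   - Follow-up interviewers are introduced to patients at baseline. This makes a returning interviewer plausible, but it is not stated.
   - The 50% is a share of assessments at risk, not of patients unblinded. Actual unblinding still requires a disclosure.

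6. **Is there a further route?** Outcome criteria has an independent interviewer rate patients' insight into their personality, at 3 and 6 months. If that person is also the follow-up interviewer, the conversation touches the subject on which the arms were treated differently. The document does not say who it is.

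7. **Caseworkers.** Where the letter is shared, the caseworker knows the content of the assessment when rating CGI, GAF and alliance. Sharing requires consent under Data handling and record keeping and is an offer under Design, although Ethical approval mentions feedback to caseworkers without that condition. The number of patients affected is therefore unknown. Staff-scored engagement is in the main outcome under Outcome criteria and absent under Outcome evaluation. Under the latter, no caseworker rating enters the primary measure.

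**The case against.** The strongest defence is that the risk is modest and already acknowledged. Both arms receive feedback, the items ask for ratings rather than content, patients are told not to disclose, and the Discussion claims only to reduce the risk. The text even mentions the outcome scales before the ratings. Interview order and an arm-guess item may sit in a fuller protocol. Most of this stands, and it rules out saying that blinding will fail or that second-wave data are unblinded. It does not remove the tension between a procedure the article states and a safeguard it states.

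Four stronger readings are tempting and are not supported:

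- **That unblinded caseworkers contradict the blinding claim.** The article never says caseworkers are blinded, and offering them the feedback is part of both conditions. Nor do all of them hold the letter.
- **That the Background documents a label bias.** It says "therapists and other professionals tend to react negatively to patients with personality disorders at an emotional level". That concerns patients with these disorders, whom randomization places in both arms. A reaction to the diagnosis in the letter is a plausible inference, but not one the document states.
- **That the Discussion bases its efficacy claim on blinded follow-up.** It bases that claim on the controlled amount of contact. Blinding is presented as a separate feature.
- **That caseworkers score the engagement component.** Outcome criteria speaks of treatment staff, and Follow-up procedure does not list engagement among caseworker ratings.

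**Conclusion.** The concern holds as an avoidable risk of unblinding. At the first follow-up the interview raises the feedback, whose content differs by arm, and so works against the non-disclosure instruction on which interviewer blinding depends.

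The second of the two primary waves is exposed if the same interviewer returns. The first is exposed as well if the ratings come before the scales. Both cases also assume that some patients disclose content. The proportion who would do so, and the direction and size of any bias, cannot be derived from the document.

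Separately, caseworker ratings of CGI, GAF and alliance are effectively open-label for patients who consent to sharing the letter. This is a limitation of those secondary data, not a breach of a stated claim. It would reach the primary outcome only if engagement stays in it and is scored by staff who have seen the letter.

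The change is worth making because it is cheap and protects the primary scales.

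**What to change.** - Collect all outcome scales (K6, OTI, WSAS, SDS, ASRS, SAPAS) before any question about the feedback.
- Have the patient complete the feedback ratings alone and seal them in an envelope, or move them to the end of the last follow-up.
- If the follow-up interviewer also rates insight into personality, do that last.
- Record the interviewer's guess of the arm at each wave, so that the blinding claim can be examined.
- Report caseworker ratings as unblinded.
- Reconcile Outcome criteria with Outcome evaluation by keeping staff-rated engagement out of the primary outcome.
- Qualify the blinding statement in the Discussion: describe the steps taken to protect it, and say that caseworkers are not blinded.

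The cost is a reordered interview form, an envelope and one guess item per wave. The downside is somewhat more incomplete rating forms when patients fill them in alone, or a longer recall period if the ratings move to the last visit. The intervention itself is unchanged.

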### Data handling and record keeping

Patient information will only be accessible to the research team. All data will be link-anonymised so that no patient identifying information will be kept with raw data. All files will be kept with the local research teams in a locked and secure cabinet. Electronic data will be stored on a central computer at the research centre.

A personal feedback letter will be given to the patient, in which the patient appears only with his or her first letter. If the patient agrees that the information in the personal feedback should be shared with the caseworker, then the same letter will be given to the caseworker. Raw data will, however, only be kept and stored by the Centre for Alcohol and Drug Research.

### Outcome evaluation

A single measure of outcome will be used as the primary outcome measure: The proportion of areas in which a 30% reduction occurred at each follow-up wave (K6, WSAS, and OTI substance use). This measure can theoretically range from -3 (deterioration in all areas) to +3 (improvement in all areas.

The data will be analyzed with mixed effects ordinal regression, using baseline values of the three outcome measures as covariates [30].

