### Randomization and blinding

Randomization will be conducted by means of a predefined list of random numbers, stratified by predefined characteristics, which will not be disclosed at this point to reduce risk of breaking of blind. Randomization is executed according to a list, the allocation sequence of which was computer-generated by one of the researchers (MH). The interviewer will be blinded to randomization at the baseline interview.

The follow-up interviewers will be introduced to the patients at the baseline interview, to assure blinded follow-up assessments.

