### Risks and anticipated benefits for trial participants and society, including how the benefits justify the risks

Patients with substance use disorders and co-morbid personality disorder experience a number of serious problems. Patients with co-morbid personality disorder tend to remain symptomatic long after treatment [7,8], and patients with some co-morbid personality disorders tend to commit a substantial amount of the crime that substance abusers commit [31].

If the findings of this study show that personality assessment can significantly improve the functioning of patients with substance use disorders, this can have significant impacts on both the quality of life of patients, and on society.

The main risk of this study is that patients experience a worsening of psychiatric symptoms or substance use as a reaction to receiving a feedback concerning their own personal functioning. There is some indication that symptoms may fail to improve with focus on personality, even if this focus improves substance use and therapeutic alliance [9]. We will monitor psychiatric symptoms every 3 months during the study, and patients have access to caseworker, psychiatrist and psychologist at the treatment centre.

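### The primary score nets improvement in one area against deterioration in another, in conflict with the stated outcome criterion, and no per-area analysis is stated that would show a mixed effect or a harm

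*Protocol article*

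**What the plan says.** All references are to the protocol article.

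- **Outcome evaluation** defines the primary measure as "The proportion of areas in which a 30% reduction occurred at each follow-up wave (K6, WSAS, and OTI substance use". It then adds: "This measure can theoretically range from -3 (deterioration in all areas) to +3 (improvement in all areas". The model follows: "The data will be analyzed with mixed effects ordinal regression, using baseline values of the three outcome measures as covariates".
- **Outcome criteria** defines the main outcome differently. A patient succeeds with a 30% decline in at least one of four areas (the fourth is treatment engagement), provided that no area deteriorates. The secondary outcomes are retention, understanding of one's own personality, and readiness to change. K6, WSAS and OTI are not listed there as outcomes in their own right.
- **Risks and anticipated benefits** gives worsening of psychiatric symptoms or of substance use as the main risk. It also reports an indication that "symptoms may fail to improve with focus on personality, even if this focus improves substance use and therapeutic alliance".
- **Randomization and blinding** says that allocation is "stratified by predefined characteristics, which will not be disclosed at this point to reduce risk of breaking of blind".
- **Inclusion criteria** asks for past-year dependence (SDS of 3 or more), not for current use.

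**The concern.** A net score gives the same value to clinically different patients. If the intervention helps substance use and does nothing for symptoms, the areas that do not respond add noise to the one that does. If it helps one area and harms another, the harm is subtracted from the benefit and may not show at all. Symptoms and substance use are the two areas that the article itself singles out, both for possible divergence and for possible harm. With no per-area analysis stated, a null result on the score could not be told apart from a mixed one.

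Two smaller matters concern the same section. A 30% decline is impossible from a baseline of 0, and neither outcome section says how such an area is scored. The model sentence also names no stratification factors, although randomisation is stratified.

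**Working it through.** The article gives no sample size, alpha, power or event rates, so there is no power figure to reproduce. The one figure to check is the range.

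**1. Range.** A proportion of three areas can only be 0, 1/3, 2/3 or 1. A sum of three areas each scored -1, 0 or +1 runs from -3 to +3, as stated. So the score nets.

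**2. What the score cannot separate.** There are 3 × 3 × 3 = 27 patterns.
- Seven score 0. One is no change in any area; six are one area better and another worse.
- Six score +1. Three (one better, two unchanged) meet the no-deterioration rule of Outcome criteria, applied to these three areas. Three (two better, one worse) fail it.

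**3. Effect on power.** Everything here is assumed: 150 per arm, two-sided 5%, independent areas, and control rates in each area of 35% improved and 15% deteriorated. OTI under treatment is 50% improved and 10% deteriorated.

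Per-area mean = p(improved) − p(deteriorated). Per-area variance = p(improved) + p(deteriorated) − mean².
- Control area: mean 0.20, variance 0.50 − 0.04 = 0.46. Score: mean 0.60, SD √1.38 = 1.175.
- Treated OTI: mean 0.40, variance 0.60 − 0.16 = 0.44.

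Power = Φ(z − 1.96), with z = difference / (mean SD × √(2/150)).

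| Effect on K6 (improved / deteriorated) | Mean difference in score | Mean SD | z | Power, net score |
|---|---|---|---|---|
| None (35% / 15%) | +0.20 | 1.170 | 1.48 | 32% |
| Fewer improve (25% / 15%) | +0.10 | 1.155 | 0.75 | 11% |
| Equal and opposite (20% / 20%) | 0.00 | 1.157 | 0 | 5% (alpha) |

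OTI improvement alone, 50% against 35%: pooled p = 0.425, so power = Φ((0.15√150 − 1.96√(2 × 0.425 × 0.575)) / √(0.35 × 0.65 + 0.50 × 0.50)) = Φ(0.676) = 75% in all three rows. At 0.05/3 (critical value 2.394) it is Φ(0.237) = 59%.

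Range for the first row: with 100 or 200 per arm the net score has 23% or 40% power, and OTI alone has 57% or 86% (40% or 74% at 0.05/3). With 150 per arm and a correlation of 0.4 between area scores, the net score falls from 32% to 20%.

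The opposite case: if all three areas gain as OTI does, the difference is 0.60, the mean SD 1.162 and z = 4.47. The net score then has 99% power (91% at correlation 0.4), above the 75% for any one area.

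**4. Strata.** Let R² be the residual outcome variance that the strata explain beyond the baseline scores (assumed 0 to 15%). In a linear approximation, omission costs 1/(1 − R²) − 1 in sample size, power is Φ((1.96 + 0.842)√(1 − R²) − 1.96), and actual type I error is 2(1 − Φ(1.96/√(1 − R²))).

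| R² | Extra patients | Power, if 80% with adjustment | Type I error |
|---|---|---|---|
| 0 | 0% | 80.0% | 5.0% |
| 5% | 5.3% | 78.0% | 4.4% |
| 10% | 11.1% | 75.7% | 3.9% |
| 15% | 17.6% | 73.3% | 3.4% |

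**The case against.** **The article does not predict opposite effects.** A reader might infer that it expects benefit on substance use to be cancelled by harm on symptoms. It does not say so. The divergence it reports is absence of improvement in one area beside improvement in another. Worsening is named as a risk in either area, not as an expected partner of benefit elsewhere. This stands: dilution is the supported reading, and full cancellation is a special case.

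**A single composite is a legitimate choice.** It needs no multiplicity correction and does well when all areas move together, as the last power calculation shows. Three corrected tests would not beat it there. The 30% cut is likewise a recognised responder rule, though it discards information. This stands against replacing the score, but not against analysing its parts beside it.

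**Component reporting is not barred.** The instruments are collected at follow-up and symptoms are monitored every 3 months. That is true, but the analysis is unstated and the areas are not among the secondary outcomes.

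**The strata may be handled elsewhere.** The factors are withheld on purpose, the model sentence does not say that its covariates are the only ones, and a fuller model may sit in an analysis plan not shown. A reader might infer that precision is certainly lost or that the test is invalid. Neither follows: the loss is nil if the strata predict nothing beyond baseline, and omission makes the test conservative.

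**Baseline zeros may be rare.** Patients are seeking treatment, and no frequency can be given. Past-year eligibility does not exclude a zero on OTI use. The article also gives no threshold for deterioration, so it is unclear whether that could be scored from 0 either.

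**Conclusion.** The point holds. The netting follows from the stated range, and it contradicts the no-deterioration rule in Outcome criteria; neither conclusion rests on an assumption. Because the article names symptoms and substance use as areas that may diverge or worsen, a mixed effect would be diluted and harm in one area could be masked.

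The size is illustrative only. For a benefit confined to OTI it is about 32% power for the net score against 59% to 75% for OTI alone, on assumed rates, 150 per arm and independent areas. The effect cancels fully only when area effects are equal and opposite.

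The strata matter is secondary: none to about 18% of patients for an assumed R² of 0 to 15%, from a linear approximation to an ordinal model. The documents do not support replacing the composite or calling the planned test invalid. This should be amended, but it does not undermine the trial.

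**What to change.** 1. Keep one primary score, and reconcile Outcome criteria with Outcome evaluation: which areas count, and whether deterioration disqualifies a patient or is subtracted.
2. Pre-specify K6, WSAS and OTI, each on its own scale at 3 and 6 months and adjusted for its own baseline, as key supporting analyses with a stated multiplicity rule such as Holm.
3. Report the number who deteriorate in each area by arm, K6 in particular, with the threshold for deterioration written down.
4. State how an area with a baseline of 0 is scored, for example as not evaluable for improvement.
5. Add to the model sentence that it is adjusted for the stratification factors. They need not be named, so the blind is unaffected.

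The cost is wording, a few more models and a multiplicity rule. No new data are needed if WSAS is taken at baseline. The Follow-up procedure section implies that it is, but Table 1 and the list under Baseline interview do not show it, so this needs confirming.
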